## Abstract

**Background:**

With the aging of society, the prevalence of hearing loss (HL) is increasing. Currently, approximately 5% of the global population has HL, and this number is projected to reach 7 million by 2050. Although hearing aids (HAs) are the primary treatment for HL, their use is limited by barriers such as high costs and social stigma. To address these limitations, over-the-counter (OTC) HAs have been introduced, but their effectiveness and drawbacks require further investigation.

**Objective:**

This study aims to conduct a noninferiority randomized controlled trial comparing OTC HAs with traditional HAs to assess the clinical effectiveness of OTC HAs.

**Methods:**

We designed a noninferiority randomized controlled trial comparing OTC HAs and traditional HAs in adults with mild-to-moderate HL. A total of 64 participants (32 per group) will be recruited. Randomization will be performed using block randomization (block sizes of 2 or 4) with an equal allocation ratio. The study will include 2 types of HAs: an OTC HA (Jabra Enhance Pro) and a traditional HA (LiNX Quattro LE561-DRW) by GN ReSound A/S. OTC HAs will be self-fitted using a smartphone app, while traditional HAs will be fitted by a licensed audiologist using the National Acoustics Laboratories–Non-Linear Prescription, second generation. Assessments, including functional gain, real-ear measurement, speech audiometry, and questionnaires, will be conducted at 6-month intervals over the course of 3 visits. Statistical analysis will compare the 2 outcomes, focusing on functional gain, to determine noninferiority.

**Results:**

This study is scheduled to begin in August 2024 and has not yet recruited any participants. The study will be conducted over 2 years, from August 2024 to July 2026. Each participant will have 2 follow-up visits at 6-month intervals, making the total follow-up period 1 year.

**Conclusions:**

Since 2022, the introduction of OTC HAs has revolutionized access to these devices. Researchers, clinicians, and the general public are keen to evaluate the clinical effectiveness of OTC HAs, as more individuals will likely use them for HL. This increased usage will provide valuable real-world data to understand the benefits and limitations of OTC HAs. Monitoring the outcomes and user feedback will provide insights into their effectiveness and impact on hearing rehabilitation.

**International Registered Report Identifier (IRRID):**

PRR1-10.2196/59894

## Introduction

### Background

As society undergoes a rapid transition toward an aging population, the prevalence of hearing loss (HL) is significantly increasing. According to the World Health Organization, approximately 5% of the global population (4.3 million individuals) currently has HL, and this number is projected to reach 7 million by 2050 [1]. One of the reasons HL has attracted attention recently is due to its association as the most modifiable risk factor for dementia [2]. Therefore, proactive hearing rehabilitation is crucial.

Hearing aids (HAs) serve as the first-line management for patients with HL. However, several barriers can prevent people from using HAs. These barriers include economic limitations such as high costs (ranging from US $3000 to US $6000 a pair), limited insurance coverage, and social stigma [3-6]. As evidence of these barriers, one study demonstrated that the rate of purchasing HAs among individuals with HL was 17.4%, whereas the use rate was merely 12.6% [7].

In an effort to increase accessibility to HAs, the US Food and Drug Administration (FDA) has recently created a regulatory category for over-the-counter (OTC) HAs. These are classified as a type of medical device that can be purchased without requiring a prescription or consultation with licensed hearing health care professionals (HHPs) [8]. Unlike traditional HAs, OTC HAs are specifically designed for adult patients with mild-to-moderate HL. The introduction of OTC HAs is anticipated to broaden access to affordable hearing care for millions of patients who currently have HL but are not adequately served by the traditional HA market.

The market for OTC HAs has been expanding rapidly. However, due to the recent FDA approval, empirical research is not available regarding their clinical effectiveness. Furthermore, OTC HAs come with multiple disadvantages that require thorough validation. One prominent drawback is that patients are responsible for fitting the HAs themselves, potentially leading to reduced accuracy in amplification [9]. In addition, the predominant older adult population, who may lack technical proficiency, may encounter difficulties in operating OTC HAs. Consequently, there is a need for studies aimed at demonstrating that OTC HAs are not inferior to traditional HAs.

To address this, we aim to conduct a noninferiority randomized controlled trial (RCT) comparing OTC HAs with traditional HAs. We hypothesize that OTC HAs will demonstrate noninferiority when compared with traditional HAs.

### Objectives

The primary objective of this study is to compare the effects of OTC HAs and traditional HAs on patients with HL. The primary outcome of interest is functional gain at the conclusion of a 1-year intervention period. Secondary objectives include assessing the impact of OTC HAs and traditional HAs on speech audiometry in both quiet and noisy environments, conducting real-ear measurement (REM), and administering questionnaires to gather additional information.

## Methods

### Study Design and Setting

In this noninferiority RCT, patients will be randomly assigned to 2 groups. The study will take place at a tertiary hospital in South Korea, serving as a single center for the research. The protocol for this study follows the guidelines outlined in the Standard Protocol Items Recommendations for Interventional Trials statement [10] (Figure 1).

**Figure 1 figure1:**
[figure not shown]
Consolidated Standards of Reporting Trials (CONSORT) diagram. HA: hearing aid; OTC: over-the-counter; PTA: pure-tone audiometry; REM: real-ear measurement; WRS: word recognition score.

### Study Population

To be eligible for this study, participants must meet specific inclusion and exclusion criteria (Textbox 1).

Inclusion and exclusion criteria.
**Inclusion criteria**
Voluntary willingness and ability to participateAged 18 years or olderProficiency in the Korean languageHearing threshold ranging from 26 dB to 55 dB (indicating mild-to-moderate hearing loss) based on the average of 4 frequencies (0.5, 1, 2, and 4 kHz) in both earsAbsence of significant abnormalities in the outer ear and middle ear as determined by otoscopyType A tympanogramNo previous history of sudden hearing loss
**Exclusion criteria**
Mental incapacity to participate in this studyPrevious use of hearing aidsAbsence of outer or middle ear diseases

### Sample Size

The number of participants for this study was determined using G*Power (version 3.1.9.4) software (Institute for Experimental Psychology). The estimated sample size was based on the findings of a previous study [11]. The calculated total sample size was 56 participants, considering an effect size (Cohen *d*) of 0.9, an error probability of .05, and a power (1– error probability) of .95. Therefore, considering an attrition rate of 15%, a total of 64 participants will be recruited, with 32 participants allocated to each group.

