### Statistical Analysis

In the descriptive analysis, continuous data will be presented using means or medians, depending on their normality. Categorical data will be quantitatively presented, including the number and percentage for each variable. For primary and secondary outcome variables, if the normality assumption is met, repeated measurements of analysis of variance will be conducted. If the normality assumption is not met, the Friedman test will be used. Independent variables will be types of HAs and time, while the dependent variables will be outcome variables. Post hoc analysis using Bonferroni correction will be conducted for significant variables. If there is no significant difference in the primary outcome of functional gain between the 2 HAs, it will be considered noninferior.

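### The stated 95% power for 56 participants rests on an unstated one-sided test and is tied neither to a noninferiority margin nor to the non-directional comparison planned

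*Protocol article*

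**What the plan says.** Sample Size (protocol article, Methods) names the software, "The number of participants for this study was determined using G*Power (version 3.1.9.4) software", and bases the estimate on an earlier study. The result follows: "The calculated total sample size was 56 participants, considering an effect size" (Cohen d) "of 0.9, an error probability of .05, and a power" given as one minus the "error probability) of .95". The paragraph does not name the test, the number of tails or a margin, and it gives no SD or raw difference in dB. Enrolment is then set: "considering an attrition rate of 15%, a total of 64 participants will be recruited, with 32 participants allocated to each group".

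Objectives and Study Design and Setting describe a two-group noninferiority trial whose primary outcome is functional gain at 1 year. Statistical Analysis says that for normally distributed outcomes "repeated measurements of analysis of variance will be conducted", with device type and time as factors. It treats the devices as noninferior if functional gain shows no significant difference between them. No noninferiority margin appears anywhere in the article.

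**The concern.** A power figure has meaning only for a named hypothesis and test. This paragraph gives a full set of inputs, but they describe a standardized difference between groups and not a deficit to be excluded. Its 95% therefore has to be matched to one of two questions: detecting a difference with the planned comparison, or ruling out a margin when the devices truly perform alike. If it fits neither without added assumptions, readers will credit the trial with a precision that it has not shown.

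The stake is larger than usual because of the decision rule. When a non-significant result counts as noninferiority, low power helps the hypothesis under test, so the power statement is the main safeguard against a false noninferiority claim.

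**Working it through.** **Inputs from the article.** d = 0.9; error probability .05; power .95; 56 evaluable; 64 enrolled (32 per arm); 15% attrition (all from Sample Size); 1:1 allocation (Assignment to Intervention Groups). Sidedness, margin, SD and within-subject correlation are not given.

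**Formula.** Two-sample t test with n per arm: df = 2n − 2, noncentrality λ = d√(n/2). One-sided power is P(T > t at 1 − α), with T noncentral t(df, λ). For a two-sided test the critical value is t at 1 − α/2 and the opposite tail is added.

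**Step 1: reproduce 56.**
- One-sided .05, n = 28: df = 54, λ = 0.9 × √14 = 3.367, critical t = 1.674, power 95.4%. At n = 27 power is 94.7%, so 28 per arm is the smallest that works: 2 × 28 = 56, an exact match.
- Two-sided .05: n = 33 gives 94.95% and n = 34 gives 95.5%, so 34 per arm, or 68. No match.
- Rank-test (Wilcoxon-Mann-Whitney) versions give 58 or 64 one-sided and 70 or 78 two-sided. None gives 56.

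**Step 2: power for the non-directional comparison.** Proxy: a two-sided .05 t test at 1 year with d = 0.9.
- 28 per arm (56): 91.1%.
- 27 per arm (54): 90.1%.

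**Step 3: power for noninferiority.** With true difference 0 and margin M in SD units, the formula is the same with λ = M√(n/2).

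| Margin (SD) | Per arm | One-sided .05 | One-sided .025 |
|---|---|---|---|
| 0.9 | 28 | 95.4% | 91.1% |
| 0.9 | 27 | 94.7% | 90.1% |
| 0.6 | 27 | 70% | 58% |
| 0.5 | 27 | 57% | 44% |

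The article sets neither these margins nor the .025 level. They show how strongly the answer depends on both.

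**Step 4: the stated decision rule.** With the Step 2 proxy and a true deficit of 0.5 SD, a non-significant result, and so a noninferiority claim, would occur 54.9% of the time with 28 per arm and 56.2% with 27.

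**Step 5: attrition.**
- 64 × 0.85 = 54.4, below 56.
- 56 / 0.85 = 65.9, so 66 enrolled.
- 56 × 1.15 = 64.4, which rounds to the stated 64, so the 15% appears to have been added to 56.
- 64 retains 56 up to a loss of 1 − 56/64 = 12.5%.
- Cost on the one-sided calculation: 95.4% − 94.7%, about 0.6 points before rounding (95.35 − 94.72 = 0.63).

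**The case against.** **The calculation may already be a noninferiority calculation.** A reader might infer from the one-sided match that this is a superiority calculation. The article does not support that. The same 28 per arm is what a noninferiority test needs with a 0.9 SD margin, true difference 0 and one-sided .05, and a one-sided test suits the stated design. On that reading the 95% would be correct. This stands as far as it goes: the superiority label is an inference. But the article calls 0.9 an effect size drawn from an earlier study, never a margin, and its decision rule uses no margin.

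**The t test is not the planned analysis.** This also stands. If the group difference were constant and averaged over three visits with equal correlation ρ between them, the effective d would be 0.9/√((1 + 2ρ)/3). Two-sided power with 28 / 27 per arm would then be 97.1% / 96.6% at ρ = 0.6, 95.9% / 95.2% at 0.7, 94.4% / 93.7% at 0.8 and 92.8% / 91.9% at 0.9. Both assumptions are ours, so it cannot be said flatly that the ANOVA needs 68. The 1-year primary endpoint makes the single-time comparison a reasonable proxy, but it remains a proxy.

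**One-sided .025 is not the article's level.** Correct. It is a common convention, which is why both levels are shown. At the stated .05, power at 0.5 SD is still only 57%.

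**Attrition.** A reader might take the enrolment shortfall as a reason why 95% is missed. It is not a material one: two participants and about 0.6 points.

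**Conclusion.** The power statement is wrong as written because it is unqualified. The figure of 56 corresponds to a one-sided .05 t test at d = 0.9. One-sidedness is inferred from the exact reproduction, not stated. The planned comparison is non-directional, and on the 1-year t-test proxy it has about 90–91% power instead of 95%; the exact ANOVA power cannot be computed from the article.

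It would go too far to say that 95% is not delivered for noninferiority. Without a margin that power is undefined. It is about 95% if 0.9 SD is the margin at one-sided .05, and falls to 70% at 0.6 SD and 57% at 0.5 SD with 27 per arm (58% and 44% at one-sided .025). What the article lacks is the link between its 95% and any stated noninferiority hypothesis. The attrition arithmetic is a genuine but minor error.

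**What to change.** Keep 64 and rewrite the Sample Size paragraph as a noninferiority calculation. State a justified margin in dB, the assumed SD of functional gain, a true difference of 0, the one-sided alpha and about 54 expected completers (64 × 0.85). Report the resulting power in place of the unqualified .95, and do not present 0.9 as an effect size unless it is declared and defended as the margin.

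In Statistical Analysis, make the primary test and its sidedness match: compare the confidence limit for the 1-year difference in functional gain with the margin, at the same alpha, in place of the no-significant-difference rule.

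Correct the attrition sentence in one of two ways: 64 enrolled with about 54 completers, or 66 enrolled for 56.

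The cost is a rewritten sample size paragraph and a revised decision rule. No extra participants are needed if 64 is kept, but the reported power will probably be less favourable.

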### Recruitment

Announcements regarding the study will be disseminated through hearing-related support groups, audiology organizations, newsletters (daily newspapers, magazines, etc), hearing clinics of primary and secondary hospitals, otorhinolaryngology outpatient clinics of a tertiary hospital, and social media platforms (Facebook [Meta], Instagram [Meta], X [formerly known as Twitter], etc). Individuals who express interest will receive information and undergo a screening test. If they meet the inclusion criteria, they will be enrolled in this study.

### Assignment to Intervention Groups

After inclusion, the patients will be randomly assigned to 1 of 2 intervention groups: OTC HAs or traditional HAs. Randomization will be performed electronically using R software (R Core Team) with block randomization and an equal allocation ratio of 1:1. The block sizes will be 2 and 4. The researchers will remain blinded to the randomization sequence. However, due to the nature of the intervention, it is not possible to blind the participants and care providers to their assigned group.

### Data Collection Methods

The results will be recorded on paper and then transferred to a Microsoft Excel document for data entry. These files will be stored as electronic records for archiving purposes.

### Data Management

The data will be securely stored on a designated server and access will be strictly controlled and limited to authorized personnel authorized by the institutional review board (IRB). Only individuals with explicit permission will have the authority to manage and access the recorded data.

### Statistical Analysis

In the descriptive analysis, continuous data will be presented using means or medians, depending on their normality. Categorical data will be quantitatively presented, including the number and percentage for each variable. For primary and secondary outcome variables, if the normality assumption is met, repeated measurements of analysis of variance will be conducted. If the normality assumption is not met, the Friedman test will be used. Independent variables will be types of HAs and time, while the dependent variables will be outcome variables. Post hoc analysis using Bonferroni correction will be conducted for significant variables. If there is no significant difference in the primary outcome of functional gain between the 2 HAs, it will be considered noninferior.

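### The Friedman fallback cannot make the between-device comparison that the same section says the analysis and the noninferiority decision rest on

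*Protocol article*

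**What the plan says.** All of the analysis text is in the Statistical Analysis section of the protocol article. The first branch reads: "For primary and secondary outcome variables, if the normality assumption is met, repeated measurements of analysis of variance will be conducted". The second branch reads: "If the normality assumption is not met, the Friedman test will be used". Both branches cover the primary outcome, functional gain at 1 year (Objectives), as well as the secondary outcomes.

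The next sentence sets out the factors: "Independent variables will be types of HAs and time, while the dependent variables will be outcome variables". Follow-up testing is conditional: "Post hoc analysis using Bonferroni correction will be conducted for significant variables". The decision rule is: "If there is no significant difference in the primary outcome of functional gain between the 2 HAs, it will be considered noninferior".

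On design, Study Design and Setting states: "In this noninferiority RCT, patients will be randomly assigned to 2 groups". Assignment to Intervention Groups specifies "block randomization and an equal allocation ratio of 1:1". Participant Timeline gives each person one device, with functional gain measured at three visits.

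**The concern.** Repeated-measures ANOVA with device type and time has a between-participant factor, a within-participant factor and their interaction. The Friedman test is a one-factor procedure for related samples. It can take the place of the time part of that ANOVA, but not of the device part or the interaction. The section therefore names a test that cannot do what its next sentence and its decision rule require.

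The trial's only confirmatory question is at stake on that branch. A significant Friedman result would show that visits differ, not that devices differ. A nonsignificant one would carry no information about a constant device difference, yet the decision rule could turn it into a noninferiority claim.

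**Working it through.** **1. The comparison that the trial was sized for.** Inputs from Sample Size: Cohen d 0.9, alpha .05 (sidedness not stated), power .95, total 56. With a two-sample t test, 28 per arm, df = 2 × 28 − 2 = 54 and noncentrality 0.9 × √(28/2) = 3.37, the one-sided power is 0.954. That gives 2 × 28 = 56 and reproduces the stated total. A two-sided test would need 34 per arm, 68 in all. The stated total thus corresponds to a comparison of two independent groups, which the fallback does not make.

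**2. What Friedman uses.** For n participants and k visits, with R_j the sum over participants of the within-person ranks at visit j:

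Q = [12 / (n k (k + 1))] × Σ R_j² − 3 n (k + 1), with k − 1 degrees of freedom.

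Here k = 3. No group label enters the formula. If every value in one arm is lowered by a constant c, each person's three values keep their order, so all ranks, all R_j and Q are unchanged. As a numerical check on 56 simulated participants, Q was 0.75 as generated, 0.75 after subtracting 100 units from one arm, and 0.75 after permuting the participants.

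**3. Other ways to apply it.** Run separately in each arm, it tests time twice and compares nothing between arms. Taking the two devices as the related samples is invalid, because different people are in each arm.

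**4. Operating characteristics.** There were 4,000 simulated trials per scenario, three visits, test level .05. The correlations and distributions are assumptions, as the documents give none.

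*Skewed data: 28 per arm, within-person correlation 0.6, exponential errors, total SD 1.*

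| Device difference (SD) | Friedman rejects | Mann-Whitney on the 1-year value rejects |
|---|---|---|
| 0 | 5.4% | 5.4% |
| 0.9 at every visit | 5.9% | 91.4% |
| 3 at every visit | 5.5% | 100% |
| 0, 0.45, 0.9 over the visits | 89% | 92% |

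In the last row Friedman is detecting a pooled time effect. It does not attribute that effect to a device.

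*Normal data: 27 per arm (64 × 0.85 = 54.4, so about 54 completers), within-person correlation 0.7.*

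| Scenario | Friedman rejects |
|---|---|
| No device difference, no trend | 5.5% |
| 0.9 SD difference at every visit | 5.6% (ANOVA group effect: 95.6%) |
| 2 SD difference at every visit | 5.2% |
| Identical devices, visit means 0, 0.3, 0.5 SD | 95.7% |

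Normal data would not trigger the fallback, so the skewed runs are the more relevant ones. Both sets agree, as step 2 requires.

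**5. A constraint on the remedy.** Participant Timeline places randomisation and fitting before the first-visit main tests, so first-visit functional gain already contains the device effect. With a constant 0.9 SD difference and correlation 0.7, adjusting for it shrinks the expected device coefficient to 0.9 × (1 − 0.7) = 0.27 SD.

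**The case against.** **The plan does intend to compare the devices.** This stands. Device type is listed as an independent variable and the decision rule refers to both devices. A reader might infer that with non-normal data the devices would never be compared. The article does not support that: it is condensed, and an analysis plan may exist. What is established is that the one test named for this branch cannot deliver the stated comparison, and that the article names no other between-arm test for non-normal data. Because the test is stated, this is a wrong choice and not a detail left for later.

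**Post hoc testing might fill the gap.** It does not clearly do so. It is limited to variables found significant, no between-group test is named, and Friedman can flag only time.

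**The branch may never be reached.** This stands in part. Functional gain is a difference between thresholds in dB, and the article gives no distributional figure for it. The bounded scores (percent-correct words, K-APHAB, K-IOI-HA) are secondary outcomes and say nothing about how likely the primary outcome is to fail the check. Still, the fallback expressly covers the primary outcome, and a conditional primary analysis has to be valid on both branches.

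**Noninferiority would not follow automatically.** This also stands. A reader might infer a near-certain noninferiority claim, but that holds only where there is no visit trend. With a shared trend, or a device difference that grows over time, Friedman rejects in about 96% and 89% of runs, and the section does not say what a time-only rejection would mean.

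**The larger fault is the decision rule.** Treating nonsignificance as noninferiority, with no margin, affects the ANOVA branch too and is a separate defect. Repairing it would not repair this one, because Friedman supplies no between-arm estimate or interval to set against a margin.

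**Conclusion.** The point holds as an internal contradiction: the fallback named for the primary outcome has no term for the factor on which the decision depends. Its blindness to a constant device difference is algebraic and rests on no assumption. The rejection rates of 5% to 6% at 0.9, 2 and 3 SD illustrate it under assumed correlations of 0.6 and 0.7. The 96% and 89% rates under a time trend depend on the trends assumed.

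If the normality check fails, the named test therefore gives no valid between-device result for functional gain. A nonsignificant outcome could be taken as noninferiority even for a much worse device, and a significant one could be misread as a device difference. The documents do not show how often this branch would be reached. It should be corrected before the analysis, because a prespecified branch of the primary analysis cannot answer the trial's question.

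**What to change.** Delete the Friedman fallback. Prespecify one between-arm analysis of 1-year functional gain, used whatever the normality check shows: for example, a linear or mixed model with device type, time and their interaction, reporting the 1-year between-arm difference with a robust or bootstrap confidence interval. Any covariate must be measured before fitting, such as unaided pure-tone average at screening, and not first-visit functional gain, for the reason in step 5 of the working.

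For the secondary scores, name in advance, outcome by outcome, which will be analysed by a between-arm rank method (Wilcoxon rank-sum with the Hodges-Lehmann difference and its confidence interval), so that no data-driven switch remains.

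The cost is protocol and analysis-plan wording only, with no change to sample size, visits or measurements. The change does not supply a noninferiority margin or replace the nonsignificance rule. Those need their own correction, and the interval produced here is what a margin would be compared with.

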### Participant Timeline

All participants will undergo in-person assessments over the course of 3 visits conducted at 6-month intervals. During the first visit, the participants will be screened and randomly assigned to 1 of 2 groups: OTC HAs and traditional HAs. Each HA will be fitted according to the guidelines described in the “Interventions” section before conducting the main tests. Subsequently, the participants will undergo main tests and be instructed to use the HA for at least 6 hours daily throughout the intervention period. After 6 months, the participants will return to the clinic for assessments using the same tests from the first visit as an intermediate evaluation. During the final visit (after 6 months), the participants will undergo the same evaluations as during the second visit and return the HAs. If participants experience any discomfort or issues with HA usage during the study period, they will be encouraged to visit the clinic at any time for adjustments (Table 1).

**Table 1 table1:** Timeline for this study.

Outcomes					Screening and baseline			After 6 months			After 1 year			
**Study consent**					✓			—^a^			—			

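### The primary outcome is functional gain at 1 year, but the noninferiority decision rests on a three-visit repeated-measures ANOVA and is not tied to the 1-year difference

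*Protocol article*

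**What the plan says.** The Objectives section sets the endpoint and its time: "The primary outcome of interest is functional gain at the conclusion of a 1-year intervention period".

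The Statistical Analysis section gives the method for primary and secondary outcomes alike: "if the normality assumption is met, repeated measurements of analysis of variance will be conducted". The factors are device type and time: "Independent variables will be types of HAs and time, while the dependent variables will be outcome variables". No covariate is listed. Follow-up comparisons are conditional: "Post hoc analysis using Bonferroni correction will be conducted for significant variables". The decision rule is: "If there is no significant difference in the primary outcome of functional gain between the 2 HAs, it will be considered noninferior".

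Under Outcome Measurements and in Table 1, functional gain is measured at all three visits: first visit, 6 months and 1 year. The Participant Timeline puts randomisation at the first visit and adds: "Each HA will be fitted according to the guidelines described in the “Interventions” section before conducting the main tests". The first functional-gain value is therefore an aided result obtained after randomisation.

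**The concern.** The Objectives ask about one visit, while the analysis section pools three. The term in a device-by-visit ANOVA that compares the two devices is the device main effect, and that is the mean of the visit-specific differences. Fitting day carries one third of its weight, although it says nothing about how a self-fitted device performs after a year of use.

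The decision rule does not resolve this. It names no visit and does not say whether the main effect, the interaction or a 1-year contrast decides. Because visit-level contrasts follow only from significant terms, a nonsignificant result can satisfy the rule without the plan guaranteeing that the 1-year estimate and its confidence interval are ever produced.

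The direction matters because the rule reads nonsignificance as success. Any dilution of a late deficit then favours a claim of noninferiority.

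**Working it through.** **Reproducing the protocol's figure.** The Sample Size section gives d = 0.9, error probability .05, power .95 and N = 56. A two-sample t test (noncentral t) with one-sided .05 needs 28 per arm, so 56 in total, with power .954. Two-sided .05 would need 34 per arm, 68 in total. The stated 56 therefore reproduces as a single two-group comparison, not as a test of a three-visit average.

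**Inputs for the check**
- From the documents: d = 0.9, used here as the 1-year deficit; three visits; 64 recruited with 15% attrition, and 64 × 0.85 = 54.4, so 27 per arm.
- Assumed: the trajectory of the deficit; between-visit correlation ρ from 0.5 to 0.9 with equal variances and correlations; two-sided .05 (the protocol does not state sidedness).

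**1-year contrast.** d = 0.9 at 27 per arm gives power .90.

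**Device main effect.** With the 1-visit SD set to 1, the variance of a participant's three-visit mean is (1 + 2ρ)/3. For a deficit growing 0, 0.45, 0.9 SD, the averaged difference is (0 + 0.45 + 0.9)/3 = 0.45 SD.

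| ρ | SD of three-visit mean | standardised difference | power |
|---|---|---|---|
| 0.5 | √(2.0/3) = 0.816 | 0.45/0.816 = 0.551 | .51 |
| 0.7 | √(2.4/3) = 0.894 | 0.45/0.894 = 0.503 | .44 |
| 0.9 | √(2.8/3) = 0.966 | 0.45/0.966 = 0.466 | .39 |

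If the deficit appears only at 1 year, the averaged difference is 0.9/3 = 0.30 SD and power is .26 to .20 over the same ρ.

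**Constant deficit.** The average stays at 0.9 SD. At ρ = 0.7 the standardised difference is 0.9/0.894 = 1.006 and power is .95, slightly above the .90 of the 1-year contrast. Nothing is diluted.

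**Device-by-time test.** For the growing deficit, the deviations from the mean are −0.45, 0, 0.45, with sum of squares 0.405. The noncentrality is (27/2) × 0.405/(1 − ρ), on 2 and 104 df. It is 10.9 at ρ = 0.5 (power .84) and 18.2 at ρ = 0.7 (power .97); at ρ = 0.9 power exceeds .99.

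**Adjustment for screening PTA.** If PTA correlates r with functional gain, adjustment multiplies the variance by 1 − r². For r = 0.3, 0.5, 0.7 that is 0.91, 0.75, 0.51, a cut of 9%, 25% or 49%. The documents give no value of r.

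**The case against.** The strongest reply is that the protocol never says the visit average decides. The rule speaks of the primary outcome, and the Objectives define that outcome at 1 year, so a reader could take the rule as the 1-year comparison. This stands: it would be wrong to report that the protocol chose the average. What remains is that the Statistical Analysis section does not fix the deciding contrast.

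Second, a device-by-time term is standard in such a model and would very probably flag a growing deficit, which could trigger the post hoc contrasts. That is correct as arithmetic. But the section neither names an interaction nor gives it a part in the noninferiority decision. One might infer from the ρ = 0.7 row that the plan would wrongly declare noninferiority 56% of the time (1 − .44); that holds only if the main effect alone decides and the deficit follows the assumed path.

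Third, no passage predicts drift. The Background's worry about self-fitting accuracy could show on fitting day, and participants may return for adjustments at any time. This also stands, and it makes the dilution conditional.

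A reader might further infer that participants with a missed visit are discarded. That is the usual behaviour of classical repeated-measures ANOVA, but the protocol does not state it, and missing-data handling may sit in documents not shown. Nor is an analysis without PTA invalid in a 1:1 randomised trial. Functional gain is already a within-person difference, and the benefit of adjustment rests on an unknown correlation.

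**Conclusion.** The concern holds in a limited form. The endpoint is fixed at 1 year, the analysis covers three post-randomisation visits, and the decision rule does not connect the two.

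If the main effect decides, a deficit growing to 0.9 SD at 1 year is detected with power .51–.39 instead of .90, and every miss is called noninferior. Those figures rest on the assumed linear trajectory, ρ of 0.5 to 0.9, 27 completers per arm and two-sided .05. They do not apply to a constant deficit or to a decision that also uses the interaction.

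Omitting PTA forgoes a precision gain of unknown size; it is not an error. The lack of a margin, and the reading of nonsignificance as noninferiority, form a separate fault: adding a margin would still leave open which difference is compared with it. This should be changed before analysis.

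**What to change.** In the Statistical Analysis section, name the OTC minus traditional difference in functional gain at 1 year as the single deciding estimate, always reported with its 95% CI. Obtain it from a mixed model for repeated measures with arm, visit and arm-by-visit, using all available visits and adjusted for the screening four-frequency PTA. Report the fitting-day and 6-month differences as secondary, not conditional on an omnibus test.

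The cost is wording only. Screening PTA and functional gain at all three visits are already collected, so no new data, visits or participants are needed.
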